2.Feasibility and acceptability of the interventions*RQ2.1*: Do child-significant other dyads accept and adhere to the intervention as measured by APCI ratings (T1, T2, and T10)?*RQ2.2*: How do the APCI raters rate the implementation of the assessment (T1, T2, and T10) and their own manual adherence?*RQ2.3*: Do the child-significant other dyads accept and adhere to the music therapy interventions (T3–T9)? Can the individual conditions of the sample in the three study arms (INMUT-KB), (MUT-K), and (WLG) be met?*RQ2.4*: How do the music therapists assess the implementation of the music therapy interventions (T3–T9) and their own manual adherence?*RQ2.5*: What additional benefits and barriers (T1–T10) result from the significant other’s participation in the child’s music therapy session? How do they perceive their participation in this research study? Do they report adverse events during the study period, and if yes, which ones?

3.Estimation of effect sizes*RQ3.1*: How likely is it that potential between-group effects of the interventions by INMUT-KB compared to MUT-K are due to the involvement of the significant others in the music therapy interaction?*RQ3.2*: What is the estimated within-subjects effect size and 95% CI for change in the proposed primary outcome, the APCI score, which encompasses measures of mutual attunement, nonverbal communication, and parental emotional response from baseline to the end of music therapy?*RQ3.3*: What is the estimated within-subjects effect size and 95% CI for change in the proposed secondary outcome, i.e. subjective goal achievement, quality of life, system-related functional level, psychosocial stress, psychosomatic complaints, and resources from baseline to the end of music therapy?

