3.Estimation of effect sizes*RQ3.1*: The potential effect of including significant others is measured using the quantitative and qualitative data of the APCI ratings, including its three subscales and the final score, at baseline (T1 and T2) and final assessment (T10)*.**RQ3.2*: The estimation of effect size and 95% CI for change will concentrate on the proposed primary outcome, i.e. APCI subscores of mutual attunement, nonverbal communication, and parental emotional response from baseline to the end of music therapy.*RQ3.3*: The estimation of effect size and 95% CI for change will concentrate on the proposed secondary outcome, i.e. subjective goal achievement, quality of life, system-related functional level, psychosocial stress, psychosomatic complaints, and resources from baseline to the end of music therapy.

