### Sample size calculation

Assuming an estimated small between-group effect size (80% power, 5% significance level), we will need 344 child-significant other dyads in a confirmatory RCT for direct comparison of INMUT-KB and MUT-K [34]. This calculation grounds in the suggestion of at least 9% of the subsequently powered RCT sample to be seen in the prior feasibility RCT. Consequently, we will recruit at least 32 child-significant other dyads. Taking the WLG into account with an additional one-third of this sample, i.e. 10 child-significant other dyads, and a drop-out rate of, again, an additional 25% in each study arm, i.e. 10 child-significant other dyads in addition, the total sample size for our feasibility RCT will include 52 child-significant other dyads (intention to treat, ITT; INMUT-KB, *n* = 21; MUT-K, *n* = 21; WLG, *n* = 10). The number of participants expected to complete the trial encompasses 40 child-significant other dyads (per protocol, PP; INMUT-KB, *n* = 16; MUT-K, *n* = 16; WLG, *n* = 8).

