#### Estimation of effect sizes

For *estimation of effect sizes*, and because child-significant other dyads treated by one music therapist (within-group) may be more like each other compared to those treated by another music therapists (within-group), a two-level linear regression analysis will be performed to account for potential clustering effects at higher levels (i.e. child-significant other dyads nested within therapists). The intraclass correlation (ICC) coefficient from the random intercept model with child-significant other dyad (Level 1) and therapist (Level 2) will be calculated for the proposed primary outcome (APCI) [59]. An ICC greater than zero will indicate a clustering effect, and any statistical analysis must be adjusted for these effects. All proposed outcomes will be analysed as intention to treat (ITT; *n* = 52) using mean scores (*M*), standard deviations (*SD*), and 95% *CI*. The ITT calculation will be regardless of whether the child-significant other dyads will violate the inclusion criteria, whether they complete the music therapy, or whether they will withdraw from the study due to protocol deviations (e.g. concurrent music therapy during the study period [60]). Missing values of less than 20% will be replaced with the conditional mean value of the subgroups (INMUT-KB, MUT-K, WLG). This will be compared to per-protocol analyses. We will use mixed-design ANOVAs (group: INMUT-KB, MUT-K, WLG; status: child-significant other dyad, child alone; time: baseline, post-intervention, 3-month follow-up), adjusting for baseline scores considering demography as well as outcome data. Because treatment outcome will be measured at three assessment points, within-group effects will be further analysed by comparisons between baseline and post-intervention (Contrast A) and by comparisons between post-intervention and 3-month follow-up (Contrast B) (RQ3.1). Effect sizes will be presented as partial eta-squared values (η^2^) and Cohen’s *d*, calculated as the difference between the means divided by the pooled standard deviation $$(d=\frac{{x}_{1}^{2}-{x}_{1}^{2}}{\sqrt{{s}_{1}^{2}+{s}_{2}^{2}}/2})$$. Classification of *effect sizes* will be as follows: η^2^ ≥ 0.010, small effect; η^2^ ≥ 0.060, medium effect; η^2^ ≥ 0.140, large effect; Cohen’s *d* 0.20, small effect; *d* ≥ 0.50, medium effect; and *d* ≥ 0.80, large effect [61] (RQ3.2, RQ3.3).

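### RQ3.1 asks how INMUT-KB compares with MUT-K, but the analyses attached to it (within-group contrasts and a three-arm ANOVA that includes the wait-list) do not isolate that difference

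*Protocol article*

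**What the plan says.** In the protocol article, Aims and objectives, RQ3.1 asks how likely it is that "potential between-group effects of the interventions by INMUT-KB compared to MUT-K are due to the involvement of the significant others" in the music therapy. RQ3.2 and RQ3.3 are worded as within-subjects effect sizes.

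Under Measures, the data for RQ3.1 are the APCI subscales and final score at T1/T2 and T10: "The potential effect of including significant others is measured using the quantitative and qualitative data of the APCI ratings".

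Under Statistical analyses, Estimation of effect sizes, the model is stated as "We will use mixed-design ANOVAs (group: INMUT-KB, MUT-K, WLG; status: child-significant other dyad, child alone; time: baseline, post-intervention, 3-month follow-up"), with adjustment for baseline. The next sentence says that "within-group effects will be further analysed by comparisons between baseline and post-intervention (Contrast A") and "by comparisons between post-intervention and 3-month follow-up (Contrast B) (RQ3.1"). This is the only place in that section where the RQ3.1 tag appears. Effect sizes are to be partial eta-squared, with 0.060 as the medium cut-off, and Cohen's d; that passage is tagged RQ3.2 and RQ3.3.

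The Sample size calculation gives 344 dyads for a confirmatory head-to-head trial of INMUT-KB and MUT-K. Innovative aspects describes the present trial as a direct comparison of the two. The abstract's Discussion says that the confirmatory sample will be calculated from the efficacy trends seen here.

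**The concern.** The added value of involving the significant other is the difference between the two active arms. The stated analyses answer two other questions. The three-arm group effect asks whether all three arms behave alike, and it is non-null whenever both therapies beat waiting by the same amount. Contrasts A and B ask whether an arm changed over time, and they are non-null under any therapy benefit, spontaneous recovery or shift in the treatment phase. Either result can be large when INMUT-KB and MUT-K are identical.

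What is at stake is the input to the next trial. That trial is a head-to-head comparison. An eta-squared carried by the wait-list, or a before-after d from one arm, is an effect size for a different comparison and would give a misleading sample size.

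**Working it through.** **1. Question against analysis**

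| Element | What it compares | Isolates INMUT-KB minus MUT-K? |
|---|---|---|
| RQ3.1 | INMUT-KB against MUT-K | This is the target |
| ANOVA group factor | INMUT-KB, MUT-K and wait-list together | No |
| ANOVA *status* factor | Dyad against child alone, not defined | Unclear |
| Contrast A | Baseline against post, within arm | No |
| Contrast B | Post against follow-up, within arm | No |
| RQ3.2, RQ3.3 | Within-subjects change | No |

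The *status* factor could mean therapy format. INMUT-KB would then always be dyad and MUT-K always child alone, so *status* would be aliased with group for the two therapy arms. The wait-list would have no level.

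**2. Contrast B against the schedule.** Table 2 has the APCI at T1-T2 and T10 only; the 3-month follow-up is a questionnaire survey. Contrast B can be formed for the secondary outcomes but not for the outcome that Measures assigns to RQ3.1.

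**3. The plan's own head-to-head figure.** The 344 dyads rest on "Assuming an estimated small between-group effect size (80% power, 5% significance level"), with no numerical d. The total from the usual two-sample formula is 2 × 2(1.960 + 0.842)²/d². Two-sided, d = 0.20 gives 786 and d = 0.30 gives 350. The d implied by 344 is 0.302, so 344 is reproduced only by a d that the text does not state. The present point does not depend on this figure, except that it is meant for INMUT-KB against MUT-K.

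**4. How far the three-arm effect can mislead.** The article gives no SDs, correlations or expected effects, so these are assumptions: SD 1 at each time; pre-post correlation r = 0.5 or 0.7; INMUT-KB exactly equal to MUT-K; both 0.5 SD better than wait-list. Arms are 21/21/10 as planned. *Status*, baseline covariates and therapist clustering are left out.

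- With two time points, group-by-time is a one-way ANOVA on change, with variance 2(1 − r): 1.0 at r = 0.5 and 0.6 at r = 0.7.
- Partial eta-squared of 0.060 corresponds to F = (0.06/2)/(0.94/49) = 1.564 on 2 and 49 df.
- Noncentrality is 0.5² × (42 × 10/52)/[2(1 − r)]: 2.02 at r = 0.5 and 3.37 at r = 0.7.
- P(eta-squared ≥ 0.060) is 50% at r = 0.5 and 64% at r = 0.7.
- When no arms differ at all, the same probability is 0.94^(49/2) = 22%. Part of the 50% to 64% is therefore small-sample upward bias; the rise above 22% is due to the wait-list.

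In simulation (20,000 runs per scenario), mean eta-squared is 0.039 with no benefit over waiting. It is 0.074 (r = 0.5) to 0.097 (r = 0.7) at a 0.5 SD benefit, although the two therapies do not differ.

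**5. Within-arm change.** The expected Contrast A difference in INMUT-KB is 0.5 SD whether the 0.5 SD is a therapy benefit or a time trend shared by all arms. The contrast cannot tell these apart, and neither version says anything about MUT-K.

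**The case against.** The strongest reply has four parts.

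*The intention is clear and the article is condensed.* Sample size calculation and Innovative aspects both name the direct comparison, and pairwise follow-up after a three-group ANOVA is commonly left to an analysis plan. Silence alone would be no finding. But the article does name contrasts for RQ3.1 and calls them within-group, so this is a stated mismatch.

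*The tag and the word 'further'.* The ANOVA sentence has no tag of its own, and the contrasts come in addition to it. Arm means, SDs and confidence intervals are promised, so the pairwise difference could be derived. That stands, but it is not named as the estimate. If the tag covers only the contrasts, RQ3.1 is left with within-arm comparisons alone.

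*The status factor may carry the comparison.* This is possible, but as written it is undefined, and on that reading it is aliased with group. It needs a definition before it can answer RQ3.1.

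*Everything is exploratory.* Aims and objectives and Biases and limitations say so, and this limits the harm. A reader might infer that the trial will falsely declare a benefit of involving the significant other, for instance from a significant omnibus test or from significance in one therapy arm only. The documents do not support that reading. They set no significance rule for this trial (the 5% level belongs to the future one), they do not propose comparing p-values between arms, and they reserve confirmatory statements for the main RCT.

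**Conclusion.** The concern holds in a limited form. None of the stated analyses isolates the INMUT-KB minus MUT-K difference that RQ3.1 asks about, and Contrast B is not available for the APCI. The consequence is a risk that the wrong effect size informs the confirmatory sample size, not a false confirmatory claim.

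The 50% to 64% against 22% is an illustration. It rests on the assumed SD, correlation and benefit over waiting, and on a simplified two-time-point model. The direction does not depend on those values: a three-arm effect can come entirely from the wait-list, and a before-after change does not compare arms.

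**What to change.** - Name one estimate for RQ3.1: INMUT-KB minus MUT-K on T10 APCI, adjusted for T1/T2 APCI, reported as a difference and as d, each with a 95% CI. Apply the therapist-clustering adjustment that the section already calls for. State that this is the effect size carried forward to the confirmatory sample size.
- Define *status*, including where the wait-list falls and how it differs from group, or drop it.
- Label the three-arm ANOVA effect and Contrasts A and B as descriptive results that do not answer RQ3.1, and restrict Contrast B to outcomes measured at follow-up.

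The cost is a change of wording, with no new data; the article reports the trial as still recruiting. The downside is that the RQ3.1 effect will usually be smaller than the omnibus or before-after effect, and its interval will include zero more often.

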**Discussion:**

This study will provide insights into the feasibility of INMUT and the final sample needed for a confirmatory RCT. We will reflect on successfully implemented study procedures and, if necessary, provide recommendations for changes considering the design, procedures, measures, and statistical analyses. The discussion will conclude with an evaluation whether a confirmatory RCT is worth the investment of future resources, including the calculated number of child-significant other dyads needed based on the efficacy trends derived from this feasibility study.

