### Randomization

#### Treatment allocation

We will use block randomization of 10 to 12 child-significant other dyads each. From the total of 52 child-significant other dyads to be included, 21 dyads will be randomly assigned to the INMUT-KB, 21 dyads to MUT-K, and 10 dyads to WLG. The randomization plan will be carried out by an independent research assistant at the Heidelberg University Hospital, who is not otherwise involved in the study, using the statistical software R version 4.2.1 [36, 37]. The randomized allocation of the child-significant other dyads into the three study arms will be performed after finalization of the screening. The allocation will be carried out by means of sealed envelopes (“sealed envelope method”), which will be opened in the presence of the child-significant other dyads together with a study staff member.

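### The printed Cohen's d formula contradicts its own verbal definition: the numerator is always zero, and the division by 2 stands outside the square root

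*Protocol article*

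**What the plan says.** Under Statistical analyses, Estimation of effect sizes, the protocol article names two effect-size measures, partial eta-squared and Cohen's d. It describes d as "calculated as the difference between the means divided by the pooled standard deviation". The formula in the same sentence is coded as "d=\frac{{x}_{1}^{2}-{x}_{1}^{2}}{\sqrt{{s}_{1}^{2}+{s}_{2}^{2}}/2" (only the brace closing the fraction follows). The values are then graded as small, medium or large at 0.20, 0.50 and 0.80, and the passage is tied to RQ3.2 and RQ3.3, which ask for effect sizes with 95% confidence intervals.

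The Discussion part of the abstract says that the trial will report the number of dyads "needed based on the efficacy trends derived from this feasibility study". Aims and objectives and the main Discussion state the same purpose. Separately, Sample size calculation gives an advance figure: "Assuming an estimated small between-group effect size (80% power, 5% significance level), we will need 344 child-significant other dyads in a confirmatory RCT".

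**The concern.** The words and the formula cannot both be followed. The formula departs from the words in two places, and the two faults differ in how easily they would be noticed.

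- **Numerator.** It carries the same subscript twice, and the terms are squared. It is zero whatever the data. Anyone who tries to use it will see this at once and repair it.
- **Denominator.** The root closes before the division by 2. The result is a plausible positive number that is too small. Someone coding from the page could mend the numerator and leave this part alone.

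Estimating effect sizes is one of the three stated aims of the trial, and d is one of only two metrics named for it. An inflated d would move effects into higher categories. If it were carried into the planning of the confirmatory trial, it would make that trial too small. Aims and objectives stresses careful estimation of case numbers in a vulnerable patient group, so this is the outcome that the feasibility study is meant to prevent.

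**Working it through.** **Inputs.** The formula, its verbal definition and the grading limits come from Estimation of effect sizes. Power of 80%, a 5% level and the figure of 344 come from Sample size calculation. The arm sizes come from Treatment allocation: "21 dyads will be randomly assigned to the INMUT-KB, 21 dyads to MUT-K, and 10 dyads to WLG". Assumptions, because the article does not give them: two-sided testing, 1:1 allocation, and true d values of 0.20, 0.30 and 0.50 as examples.

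**Step 1: does the plan's own figure of 344 depend on this formula?** The article states a small effect without a number, so 344 cannot be reproduced outright. Normal approximation per arm: n = 2(1.960 + 0.842)² / d².

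- d = 0.20, two-sided: 393 per arm, 786 in total (t-based 788). One-sided: 620 in total.
- d = 0.30, two-sided: 175 per arm, 350 in total (t-based 352). This is close to 344.
- The d implied by 172 per arm is 2.802 × sqrt(2/172) = 0.302.
- d = 0.20 × sqrt(2) = 0.283: 394 in total two-sided, 310 one-sided. Neither is 344.

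So an assumed d near 0.30 comes close to 344, and the misplaced 2 does not explain it.

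**Step 2: numerator.** x1² − x1² = 0 for any data. Literally, d = 0 and no sample size can be derived from it.

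**Step 3: denominator.** Printed: sqrt(s1² + s2²)/2. Root of the mean variance: sqrt((s1² + s2²)/2). The second divided by the first is sqrt(2) = 1.414 for any pair of SDs:

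| s1, s2 | printed | root mean variance | ratio |
|---|---|---|---|
| 1, 1 | 0.707 | 1.000 | 1.414 |
| 1, 2 | 1.118 | 1.581 | 1.414 |
| 5, 12 | 6.500 | 9.192 | 1.414 |

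For 21 against 21 the root mean variance equals the pooled SD, so the factor is exact there. For 21 against 10 the pooled SD is sqrt((20 s1² + 9 s2²)/29). With SDs 1 and 2 it is 1.390, a ratio of 1.24 to the printed denominator. With SDs 2 and 1 it is 1.752, a ratio of 1.57. With equal SDs the ratio is again 1.414.

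**Step 4: effect on the labels if only the numerator is mended (equal arms).** 0.20 becomes 0.283, 0.30 becomes 0.424, and 0.36 becomes 0.51. The medium limit of 0.50 is reached from a true 0.50/1.414 = 0.354, and the large limit of 0.80 from a true 0.80/1.414 = 0.566.

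**Step 5: effect on a between-group sample size planned from that d.** N is proportional to 1/d², so it falls by a factor of 2.

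| true d | N needed (normal approximation) | N planned from inflated d | true power |
|---|---|---|---|
| 0.20 | 786 | 394 | 0.51 |
| 0.30 | 350 | 176 | 0.51 |
| 0.50 | 126 | 64 | 0.52 |

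The t-based totals are 788 against 396 for d = 0.20, and 352 against 178 for d = 0.30. Check of the power at d = 0.20 with 197 per arm: 0.20 × sqrt(197/2) = 1.985, and 1.985 − 1.960 = 0.025, which gives power of 0.51.

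**The case against.** The strongest reply is that this is a misprint. The verbal definition in the same sentence is right, and a numerator that is impossible on its face marks the whole display as corrupted. Nothing shows that the analysis would use the faulty denominator, and Biases and limitations calls all analyses descriptive and exploratory. Much of this stands. A misprint is the likelier explanation, and it limits what can be said about consequences. It does not remove the error. The braces in the coded formula are intact and the root closes before the 2, so this is not a bracket lost in reading the file. Nor is the formula a detail left to an analysis plan, because the article chose to print one.

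A reader might infer more: that the trial's d is overstated by 41% and that the confirmatory sample size is halved. The article does not support this, for four reasons.

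- A d that is always zero is not overstated. The 41% needs a half-repair that nobody has announced.
- The only confirmatory figure given, 344, rests on an effect assumed in advance and not on this formula.
- The article says that the later number will come from this trial's results. It does not say that this d is the input, and partial eta-squared is also to be reported.
- RQ3.2 and RQ3.3 ask for within-subjects effects, whereas the sample sizes above are for a comparison between two groups. A within-subjects d would not enter that calculation directly.

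It is also fair to say that an unweighted mean of the variances is adequate for INMUT-KB against MUT-K at 21 each. Weighting matters only for contrasts with the wait-list group, and only when the SDs differ.

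**Conclusion.** The formula is wrong as written, in numerator and denominator, and conflicts with the correct words that introduce it. That much needs no assumption.

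Its consequence is conditional. If the numerator alone were repaired, d would be too large by a factor of exactly sqrt(2) for equal arms. A between-group sample size taken from that d would be about half of what is needed, with true power of about 51% to 52% for the effects examined. These figures assume two-sided 5% testing, 80% intended power, 1:1 allocation and direct use of d in the planning. No number now in the article is changed by the error. It should be corrected before the analysis, because this is the stated rule for one of the trial's main outputs.

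**What to change.** Replace the formula with

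d = (mean1 − mean2) / s_pooled, where s_pooled = sqrt{[(n1 − 1)s1² + (n2 − 1)s2²] / (n1 + n2 − 2)}.

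For the 21 against 21 comparison this reduces to sqrt((s1² + s2²)/2), and it also serves the 21 against 10 contrasts. Check that the analysis code computes this quantity before any effect size is produced. A small-sample correction, the choice of standardiser for pre-post change and the interval method are matters for the analysis plan and are not needed to mend this error.

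The cost is one line in an erratum or in the analysis plan, plus a code check. The article gives the trial as still recruiting, so the change needs no new data and places no burden on families.

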### Biases and limitations

This study is a feasibility RCT with interest in carefully planning the subsequently confirmatory RCT. All statistical analyses will be descriptive and exploratory with the aim of obtaining data that can be used to design a confirmatory RCT. Consequently, the main RCT is necessary before a confirmatory statement about the effectiveness of interaction-focused music therapy for children with cancer and their significant other can be made reliably. Though this is an assessor-blind study, children and their significant other, as well as the therapists, will be informed about which study arm they will be allocated to. This however is a naturalistic fact of “real-world delivery of care” ( [64] p. 6). We try to balance direct and indirect allegiance by conducting the music therapy sessions by equally educated music therapists from the different clinics on the group level and implementing high methodological quality that appears to buffer allegiance [39]. However, due to the small sample size, we will not be able to perfectly control for allegiance effects.

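### Uncorrected partial eta-squared is labelled from its point estimate: with no effect, the three-arm group effect in 52 dyads would be called small or larger about 78% of the time

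*Protocol article*

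**What the plan says.** Under Estimation of effect sizes, the protocol article sets the analysis population: "All proposed outcomes will be analysed as intention to treat (ITT; *n* = 52", with a comparison against the per-protocol set. The model is a mixed-design ANOVA: "We will use mixed-design ANOVAs (group: INMUT-KB, MUT-K, WLG; status: child-significant other dyad, child alone; time: baseline, post-intervention, 3-month follow-up". The estimators follow: "Effect sizes will be presented as partial eta-squared values (η^2", together with Cohen's d. Verbal labels are then assigned: "η^2^ ≥ 0.010, small effect; η^2^ ≥ 0.060, medium effect", and "η^2^ ≥ 0.140, large effect"; for d the cut-offs are 0.20, 0.50 and 0.80. That sentence closes with a reference to RQ3.2 and RQ3.3. Both questions ask for a within-subjects effect size for change, with a 95% CI.

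Allocation is unequal: "21 dyads will be randomly assigned to the INMUT-KB, 21 dyads to MUT-K, and 10 dyads to WLG".

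Two statements govern how the results will be used. Biases and limitations says: "All statistical analyses will be descriptive and exploratory with the aim of obtaining data that can be used to design a confirmatory RCT". The Discussion part of the abstract promises an "evaluation whether a confirmatory RCT is worth the investment of future resources", and says the number of dyads for that trial will be calculated from the efficacy trends seen here.

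**The concern.** Sample partial eta-squared cannot be negative, so it exceeds zero on average even when the true effect is zero. The excess grows with the numerator degrees of freedom and shrinks with the sample size. With three arms and 52 dyads it is large compared with a cut-off of 0.010. A label read off the point estimate then says little about whether there is an effect, and it overstates the size.

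Cohen's d has no comparable bias here, but it is imprecise: its standard error at 21 versus 21 is larger than the small cut-off of 0.20.

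What is at stake is the planning value of the results. If the reported magnitudes are inflated and the between-group ones carry no interval, they are a poor basis for judging or sizing a confirmatory trial.

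**Working it through.** **Inputs.** All come from the protocol article: N = 52 in arms of 21, 21 and 10 (Treatment allocation); 40 expected completers, 16 + 16 + 8 (Sample size calculation); cut-offs 0.010, 0.060 and 0.140; three groups; three time points for the questionnaires. Table 2 schedules the APCI at T1–T2 and T10 only, so it has two time points (baseline and end of therapy).

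**The plan's own figure.** 32 + 10 (wait-list) + 10 (dropout allowance) = 52. This reproduces. The plan gives no figure for how the labels behave.

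**Distribution with no effect.** With independent normal errors, sphericity and no clustering, partial eta-squared follows Beta(df1/2, df2/2), with mean df1/(df1 + df2).

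*Three-arm group effect, N = 52.* df = 2 and 49. The same df apply to group-by-time with two time points, as for the APCI.
- Mean = 2/51 = 0.039, about four times the small cut-off.
- P(≥ c) = (1 − c)^(49/2).
- Small or larger: 0.99^24.5 = 0.782.
- Medium or larger: 0.94^24.5 = 0.220.
- Large: 0.86^24.5 = 0.025.
- A simulation with arms of 21, 21 and 10 (100,000 runs) gave 0.781, 0.220 and 0.025.

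*Other planned effects, same method.*

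| Effect | df | P(≥ 0.010) | P(≥ 0.060) |
|---|---|---|---|
| Time, two points, N = 52 | 1, 49 | 0.485 | 0.083 |
| INMUT-KB vs MUT-K, 21 vs 21 | 1, 40 | 0.529 | 0.118 |
| Time, three points, N = 52 | 2, 98 | 0.611 | 0.048 |
| Group-by-time, three points, N = 52 | 4, 98 | 0.911 | 0.190 |
| Group, per protocol, N = 40 | 2, 37 | 0.830 | 0.318 |

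The three-point rows apply to the questionnaire outcomes only. Adjusting for covariates barely moves the 0.782: it becomes 0.786 with one covariate and 0.802 with five (an assumed number).

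**Cohen's d, INMUT-KB versus MUT-K.** SE with no effect = √(1/21 + 1/21) = 0.309. P(|d| ≥ 0.20) is the two-sided t probability on 40 df at 0.20/0.309 = 0.648, which is 0.52. If the true d is 0.20, the same probability is 0.60. The small label therefore barely separates the two cases.

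**With bias correction.** For df 2 and 49, omega-squared = 2(F − 1)/(2F + 50). It reaches 0.010 when F ≥ (2 + 0.5)/(2 − 0.02) = 1.263. With no effect, P(F ≥ 1.263) = (1 + 2 × 1.263/49)^(−24.5) = 0.29. Medium or larger falls to 0.08 and large to 0.01. Simulated epsilon-squared gives nearly the same rates (0.29, 0.08 and 0.01).

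**The case against.** The strongest reply is that the labels are conventional descriptors of magnitude, not a test. The study declares its analyses descriptive and exploratory and says the main trial is needed before any confirmatory claim. Its one explicit numerical success criterion concerns recruitment and retention. The labels cite RQ3.2 and RQ3.3, which concern within-subjects change and come with 95% CIs, and for a two-point change the null rate is about 49%. The choice of estimator could also be seen as detail for an analysis plan that is not shown.

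Much of this stands, and it rules out three stronger readings that a reader might infer:
- That 78% describes the planned analyses in general. It does not: it belongs to effects with 2 and 49 df, and the N = 52 rates and the two-arm contrast run from about 49% to 91%.
- That the labels form a detection rule or a go/no-go rule. No section makes a label trigger anything; the abstract links the confirmatory trial to efficacy trends, not to labels.
- That the cut-offs themselves are too low. The cause is the upward bias and imprecision of the estimates at this sample size.

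What the reply does not answer is that the article itself names the uncorrected estimator and its cut-offs, so this is not a detail left open. The stated CIs cover within-subjects change and outcome summaries. None is stated for a between-group effect size, although INMUT-KB versus MUT-K is the comparison on which the confirmatory trial is sized. Exploratory status does not make a biased estimate a sounder planning value.

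**Conclusion.** The point holds in a limited form. For the three-arm group effect, and for group-by-time with two time points, uncorrected partial eta-squared in 52 dyads averages 0.039 with no effect. It earns a small or larger label about 78% of the time and medium or larger about 22%. For INMUT-KB versus MUT-K the small-or-larger rate is about 53% by eta-squared and 52% by d. For two-point change it is about 49%.

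These rates rest on normal data, sphericity, complete data and no clustering within therapists.

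This is a weakness in how effect sizes are reported and carried into planning. The documents do not show that a false claim of efficacy would follow.

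**What to change.** In Estimation of effect sizes:
1. Replace partial eta-squared with partial omega-squared or epsilon-squared.
2. Give a 95% CI with every effect size, including the INMUT-KB versus MUT-K contrast.
3. State any small, medium or large label for the two CI limits instead of for the point estimate alone.
4. Say that the worth and size of the confirmatory trial will be judged from the interval, not from the label.

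Replacing d with Hedges' g would change little: the correction factor at 21 versus 21 is 0.98. No rule about whether an interval includes zero is needed; that would bring a significance test into a descriptive study.

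The cost is a few sentences and a few lines of code, with no new data. Reported effect sizes will be smaller and fewer will carry a clear label. About 29% of null three-arm group effects would still reach 0.010 after correction, which is why the intervals are needed as well.
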